### Methods in analysis to handle protocol non-adherence and any statistical methods to handle missing data {20c}

Depending on the assumed missing data mechanism, two robust models will be considered to address missing data, specifically missing data at random (multiple imputation; see Taljaard et al. [53]) and missing data not at random (selection model; [54]).

To address a lack of adherence (i.e., kindergartens are randomized to receive the *Nor-SSEL* but still need to implement it integrally over the 28 weeks), we will use an approach called the Complier-average causal effect [55, 56], which gives an unbiased estimation of the effect of the intervention when nonadherence under different assumptions is considered (see Little & Yau [57]), especially under a multilevel design [50], as in the current study.

### Plans to give access to the full protocol, participant-level data, and statistical code {31c}

All components of this research, including but not limited to the research protocol, fully anonymized datasets, code, and data analyses, will be made available on the Open Science Framework. Project outcomes will be shared through peer-reviewed publications and actively disseminated to government officials, policymakers, NGOs, and communities within Norway and globally.

#### Oversight and monitoring

### Composition of the coordinating centre and trial steering committee {5d}

The Trial Scientific Steering Committee (TSC) will include all the authors listed in this protocol paper. All the authors will be responsible for the scientific conduct of the trial under the leadership of Author [name]. Additionally, a Trial Project Management Team will oversee the trial’s day-to-day operational requirements. Additionally, chaired by [name], this team will include the first, fifth, sixth, and seventh authors, as well as at least one additional senior adviser from the Section for Research Administration at Østfold University College.

### Composition of the data monitoring committee, its role and reporting structure {21a}

The project management acts as the data monitoring committee, which is led by the fifth author. Deidentified data will be made available upon request. There are no competing interests or sponsor conflicts.

### Adverse event reporting and harms {22}

This RCT is considered low-risk, non-invasive, and non-clinical. It is implemented by kindergarten teachers in a class environment where activities are planned and discussed with the research team as per the protocol. Teachers can cease implementation at any time if they consider the program to be ineffective or if it creates undue harm. Furthermore, no adverse harms were reported in the cluster of RCTs involving SEL skills in the systematic review and meta-analysis by Cipriano et al. [1].

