### Objectives {7}

In the current trial, we plan to use a cluster randomized controlled design to compare the effectiveness of Nor-SSEL versus free play on SEL in kindergartens. The primary research question is: Is Nor-SSEL more effective than free play in enhancing children’s social-emotional learning (SEL) and empathy? Our hypothesis states that Nor-SSEL is superior to free play in enhancing children’s social-emotional learning (SEL) and empathy.

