### Trial design {8}

This study is a cluster randomized controlled trial. The intervention group will receive Nor-SSEL for 28 weeks, and the control group will receive added playtime, with a 1-year follow-up (6 months after the transition from kindergarten to school).

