### Criteria for discontinuing or modifying allocated interventions {11b}

Parents may withdraw their consent at any time without affecting their participation in the main study; however, the intervention and control conditions are part of the kindergarten’s core educational activities. If needed, kindergartens and parents need to seek alternative arrangements for the child during the intervention/control activity. Kindergarten staff will report instances where the study is suspected to worsen the child’s functioning and well-being, in which case the project’s designated clinical specialist will be contacted.

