### Provisions for post-trial care {30}

Our team has a clinical specialist in child and adolescent psychiatry, specialized in early childhood mental health, who will provide support during the study, dealing with situations where atypical scores not previously reported by the parents could indicate that children are at risk for mental health problems. The specialist will be available throughout the study, i.e., for at least 1 year following intervention completion. The risk of participants experiencing adverse events during this trial because of the interventions is very low. However, we will employ safeguarding procedures to mitigate the risks of adverse effects by the specialist in child and adolescent psychiatry. The responses in the SDQ will be screened for atypical scores indicating risk for mental health problems. Where any participant discloses information that shows them or others to be at risk of significant harm, the research team will make direct referrals to relevant service providers. The referral process will be triggered through survey responses that indicate potentially harmful experiences and/or support needs (e.g., high scores on the SDQ scale). Direct referrals to in-person social services will also be available if parents request them to do so.

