## Assignment of interventions: blinding

### Who will be blinded {17a}

Researchers will be blinded to the link between kindergarten and the assigned randomization until the baseline is assessed. After that, the research team will know the kindergarten’s random status and allocate them to receive the training in the Second Step. Blinding informants in this context is not possible. Participants are not masked to the intervention status; teachers and parents are the primary informants of the outcomes.

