#### Data collection and management

### Plans for assessment and collection of outcomes {18a}

Only quantitative data, based on scales and questionnaires, will be collected throughout the one-and-a-half-year follow-up period. All outcomes of intervention effectiveness will be measured at baseline, immediately after the 28 weeks of the intervention, and 7 months after transitioning to the first grade (approximately 1 year after the intervention’s completion). Math and reading grades will be collected at the end of the first grade.

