### Interim analyses {21b}

N/A: No interim analyses are planned for this study.

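### The harms section lets teachers stop delivery because they judge the programme ineffective, which is the trial's own question and not a harm

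*Protocol article*

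**What the plan says.** Adverse event reporting and harms {22} gives two separate grounds for stopping, joined by *or*: "Teachers can cease implementation at any time if they consider the program to be ineffective or if it creates undue harm". No other section limits or withdraws this permission.

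The surrounding plan is as follows.

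- Objectives {7} makes effectiveness the research question: "Our hypothesis states that Nor-SSEL is superior to free play in enhancing" social-emotional learning and empathy.
- Trial design {8} fixes the exposure: "The intervention group will receive Nor-SSEL for 28 weeks, and the control group will receive added playtime".
- Strategies to improve adherence {11c} sets up teacher logs, app tracking of completion, and modules that open and lock so that the curriculum is followed in order.
- Section {20c}, on non-adherence, counts a Nor-SSEL kindergarten that does not deliver the programme in full over the 28 weeks as non-adherent, and plans a complier-average causal effect analysis for it.
- The Discussion calls for consistent delivery across sites, with training, close monitoring and operating procedures that support fidelity.

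**The concern.** A harms section should say when delivery stops to protect children. A teacher's view that the programme is not working is a different matter: it is a mid-course answer to the trial's own question, given kindergarten by kindergarten and without a criterion. The protocol thus permits in one section what it calls non-adherence in another and invests effort in preventing elsewhere.

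*The program* most naturally means Nor-SSEL, since {11c} says the control condition has no pre-structured programme. As worded, the permission therefore seems to fall on one arm.

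What is at stake is dose. A stop on this ground can only shorten the Nor-SSEL exposure. If the kindergartens that stop would have gained from continuing, the difference between arms shrinks and power falls. A null result would then leave open whether the 28-week programme does not work or was not delivered for 28 weeks.

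**Working it through.** **Inputs from Sample size {14}.** 30 kindergartens of 15 children per arm (450 children per arm), SD 1, ICC 0.065, coefficient of variation of cluster size 0.65, two-sided alpha 0.05, power 80%, stated detectable difference 0.27. The recruited number is 66 kindergartens (33 per arm, 495 children per arm); the extra six are for attrition.

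**Step 1: reproduce the plan's figure.**

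- Design effect with equal clusters: 1 + 14 × 0.065 = 1.91.
- Relative efficiency for unequal clusters: 1 − CV² × λ(1 − λ), with λ = 15 / (15 + 0.935/0.065) = 0.5105. This gives 1 − 0.4225 × 0.5105 × 0.4895 = 0.894.
- Design effect: 1.91 / 0.894 = 2.135.
- Standard error of the difference: √(2 × 2.135 / 450) = 0.0974.
- Detectable difference at 80% power: 2.80 × 0.0974 = 0.273, against 0.27 stated. The figure is reproduced.
- Power at exactly 0.27: Φ(0.27/0.0974 − 1.96) = 0.79. A noncentral t calculation with degrees of freedom based on children also gives 0.79.

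**Step 2: what stopping could do (illustration only).** The documents give no stopping rate and no retained effect, so three quantities are assumed:

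- f, the share of Nor-SSEL kindergartens that stop: 0.1, 0.2 or 0.3 (3, 6 or 9 of 30).
- Half of the effect is lost in a kindergarten that stops.
- k, the effect those kindergartens would have had under full delivery, relative to the average: 1, 0.5 or 0.

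Taking 0.27 as the effect under planned delivery, the diluted difference is d = 0.27 × (1 − 0.5 × f × k), and power = Φ(d/0.0974 − 1.96).

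| k | f = 0.1 | f = 0.2 | f = 0.3 |
|---|---|---|---|
| 1 (stops unrelated to true benefit) | d 0.257, power 0.75 | d 0.243, power 0.70 | d 0.230, power 0.65 |
| 0.5 | d 0.263, power 0.77 | d 0.257, power 0.75 | d 0.250, power 0.73 |
| 0 (those that stop would not have benefited) | d 0.27, power 0.79 | d 0.27, power 0.79 | d 0.27, power 0.79 |

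**Step 3: all 66 kindergartens kept.** The standard error is √(2 × 2.135 / 495) = 0.0929. Power is 0.83 with no stops and, at k = 1, 0.79, 0.74 and 0.70. A full sample would offset some of the loss, but the protocol sets that margin aside for attrition and not for shortened delivery.

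**The case against.** The strongest case against is that incomplete delivery is already foreseen. Section {20c} names the event and plans an analysis for it, {11c} tracks it, and a protocol may allow discontinuation and still count it as non-adherence. This is an effectiveness trial, and teachers dropping a curriculum they find unhelpful is part of real-world effectiveness. Nothing shows that deleting a few words would make a teacher continue, and the power figures describe assumed non-adherence in general, not the effect of this sentence.

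Much of that stands. The stopping that the sentence adds is unknown, and if teachers judge well the loss is small or nil. Two things remain. The complier-average analysis estimates a different effect and does not restore dose or power in the as-randomised comparison. And the protocol's own position on delivery is full and consistent, not optional.

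Three stronger readings are tempting and are not supported:

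- **That {22} contradicts {11b}.** Section {11b} concerns the individual child: consent withdrawal, and "Kindergarten staff will report instances where the study is suspected to worsen" that child's functioning, after which the clinical specialist is contacted. It is not a competing list of grounds on which a teacher ends delivery.
- **That the result is biased because the people who may stop also rate the outcome.** The protocol does say "Participants are not masked to the intervention status; teachers and parents are the primary informants of the outcomes". But a stop leaves the kindergarten in its randomised arm, and the permission to stop does not bias that comparison. Lack of masking is a separate matter and adds nothing here.
- **That the permission amounts to an unplanned interim look.** The statement "No interim analyses are planned for this study" refers to statistical analyses. A teacher's classroom decision is not one.

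**Conclusion.** The point holds in a limited form. The harms section gives a stopping ground that is not a harm, that rests on the trial's own question, and that authorises what the protocol elsewhere counts as non-adherence. The as-randomised comparison remains unbiased. The possible cost is a diluted contrast and a null result that is harder to interpret for the 28-week programme.

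A reader might infer from the table that power will fall to 65%. The documents do not support that. It needs 30% of Nor-SSEL kindergartens to stop, half the effect to be lost in each, and teachers' judgement to be unrelated to true benefit. Over the assumed range, power lies between 79% (no loss) and 65%. How much of any such stopping this wording would cause cannot be found from the documents. This is a cheap improvement, not a flaw that threatens the trial.

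**What to change.** In Adverse event reporting and harms {22}, delete perceived ineffectiveness as a ground for stopping. Keep the harm ground as it is, with no added step before a teacher may stop for harm, and word it to apply to both arms.

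Two sensible accompaniments use what is already in place:

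- Record the date and reason of any stop in the existing app.
- State that stopped kindergartens stay in the scheduled T2 and T3 assessments and are analysed in their allocated arm. Section {18a} already schedules these for every outcome: "All outcomes of intervention effectiveness will be measured at baseline, immediately after the 28 weeks of the intervention" and again after the move to first grade.

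The cost is a change of wording. Its downside is slightly less stated discretion for teachers. The right to stop for harm and the right to withdraw consent are untouched. The Trial status section describes a version 1 protocol that was not yet recruiting, so the change fits best before delivery begins.

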### Frequency and plans for auditing trial conduct {23}

Our project has no independent auditing process. A project management team and data management team, composed of a multidisciplinary team of experts (biostatisticians, educators, computer science experts, and kindergarten teachers), meet biweekly and hold joint monthly meetings to monitor trial conduct and data quality. The TSC provides oversight through its annual meetings.

### Plans for communicating important protocol amendments to relevant parties (e.g., trial participants, ethical committees) {25}

Substantial protocol amendments will be communicated to the research ethics committee of the Østfold University College, as well as the TSC and relevant online trial registry. Should such amendments concern study participants, they will be communicated through the local implementing partners, and additional consent will be sought where necessary. Non-substantial amendments will be kept on record.

### Dissemination plans {31a}

The results will be disseminated through academic publications to ensure peer review of the findings and their interpretation; we anticipate three main publications: (1) the effectiveness manuscript focused on the effects of the intervention on the outcomes and the distal exploratory measure, (2) the mediation focused manuscript targeting a closer and longer effect of intervention (based on serial mediation modeling), and (3) a cross-lagged panel model effect between empathy and SEL skills. The findings will be widely disseminated within Norway to education and health policy audiences, participating schools, and relevant professional associations. International dissemination will be achieved primarily through academic conferences and publications.

## Discussion

We believe that the Nor-SSEL will impact the SDQ and EmQue scores and the joint attention score. This study contributes to the scientific understanding of how such interventions can impact SEL and future academic achievement in kindergarten-aged children and provides insights into mechanisms through which interventions such as Nor-SSEL in early childhood might aid in the development of SEL. This could shape early education policies and practices and even their potential transposition to academic skills in the first grade. This study involves several logistical and coordination challenges, particularly related to participant recruitment and the risk of attrition during the transition from kindergarten to school. Strategies have been designed to address potential challenges in recruiting kindergartens and children through active recruitment until we reach sufficient participation.

Delivering the Nor-SSEL consistently across study sites requires thorough personnel training and close monitoring. Standard operating procedures following the guidebook and the web application are in place to support fidelity to the intervention protocol. Additionally, thorough training and follow-up will be provided to the active control condition to support the integrity of the condition. Site coordination is managed through biweekly project management meetings and monthly cross-functional team meetings. This structure is intended to facilitate communication and early identification of potential issues.

Missing data and data management are issues we have addressed by robust data quality assurance procedures using a web application with timely prompts to ensure data completeness and accuracy. Using the web application and Nettskjema, we seek to streamline data collection while minimizing the burden on staff and parents.

Specific attention has been given to ensuring ethical compliance and participant understanding. Input from community representatives, professionals, ethics advisors, and researchers has been integrated into the study. The control condition is considered meaningful, considering the ongoing discussion in the Nordic setting on using standardized pedagogical programs as part of the core educational activities.

### Trial status

Protocol version number: 1. June 4th 2025. Not yet recruiting. Recruitment begins August 2025 and will be completed by June 2026.

## Data Availability

Data sharing is not applicable to this article, as no datasets were generated or analyzed. Some datasets generated by the study will be made available via an open-access repository once fully anonymized and after the main study findings have been published.

## Abbreviations

No-SSEL: Norwegian version of Second Step Early Learning
SEL: Socio-emotional learning
RCT: Randomized controlled trial
SDQ: Strength and Difficulties Questionnaire
EmQue: Empathy Questionnaire for Children
RCN: Research Council of Norway
SES: Socioeconomic status
GDPR: General Data Protection Regulation
WLSMV: Diagonally weighted least squares
TSC: Trial Scientific Steering Committee
PRE-FER: Institutional ethical advisory commission at Østfold University College
REC: Regional Ethics Committee
